## Methods/Design

A time-series embedded mixed method design will be used to achieve the study purpose and aims. In a time series design, baseline and outcome variables are measured, the intervention (LWHP) is applied to all subjects, and they are followed over time with repeated measures of outcome variables [25]. A time series design was chosen instead of an experimental design because the purpose of the proposed research is to explore the mechanisms or causal processes of the LWHP. This is accomplished through path analysis in which experimental designs are not typically used [26]. The time series design was also chosen because of the ethical issues of assigning subjects to a control group when the intervention has shown potential benefits. In the pilot study of the LWHP, qualitative data suggests that the LWHP has positive benefits [7]. Harding and Higginson [27], in a systematic review of interventions in palliative care suggested that interventions should be evaluated using repeated measures from baseline and that ideal randomized controlled trials (RCT) may be inappropriate. These design recommendations were supported by Grande and Todd [28] following their review of RCTs in palliative care research. Grande and Todd also recommended using mixed method designs (quantitative and qualitative) to improve interpretation of the results.

Baseline hope, quality of life, loss/grief, and self-efficacy data will be collected before the subjects receive the LWHP. These measures will then be repeated at 1 and 2 weeks, 3, 6, and 12 months. Health services utilization data will be collected from the Saskatchewan Health Administrative Database for all subjects one year prior and one year after study enrolment.

One aspect of the LWHP asks subjects to keep a journal of their challenges and what gave them hope each day. This narrative qualitative data will be collected for the first 2 weeks as part of the intervention and analyzed to inform the quantitative data regarding the mechanisms involved in the LWHP. In this way, the collection of the qualitative data will not interfere with the LWHP mechanisms but inform it. The quantitative and qualitative data are collected concurrently with the quantitative being the predominant design to gain perspectives from the different types of data [29].

By analyzing hypothesized causal processes or pathways of the LWHP conceptual model, information is being collected about the intervention and underlying theory. If for example, the study findings are positive and the data supports the conceptual framework our understanding of an important psychosocial resource will be increased. If the findings do not support the model, the underlying theory and the LWHP will be revised to be more effective.

### Intervention: Living with Hope Program

The LWHP is theory based, focuses on the caregivers themselves and has been pilot tested. The LWHP consists of the Living with Hope film featuring caregivers of patients with advanced cancer describing their hope and a hope activity "Stories of the Present." Following viewing of the film with trained research assistants (RAs), (without discussion) the RA's instruct the subjects to take 5 minutes at the end of the day and write about their thoughts, challenges and what gave them hope over a 2 week time period. Subjects can choose to use a journal, a computer or audiotape their journals. Dosage of the LWHP is being determined by the number of journal entries and the amount of time spent on the journal. From the pilot study, compliance over a 2 week time period was 79% for number of journals and 100% for expected time. The issue of dosage and compliance is monitored in this study as it is unknown if it has an impact on the study outcomes. Variation of the dosage is expected and will be accepted in this study as this is the reality of clinical practice [10]. The 2 week length of time journaling is based on a review of journaling studies and older adults which suggests that the optimum length of time for journals is between 1 and 2 weeks [30]. We recognize that subjects may wish to continue journaling past 2 weeks if they find it beneficial. Although studies have described the benefits of journaling, the effect of the length of time journaling as a variable affecting outcome has not been supported [31]. However, it is a variable that will be monitored for its effect throughout this proposed study. If there is a significant relationship with any of the variables it will be added to the statistical analysis of conceptual framework. The possibility of co-interventions occurring such as counseling and support programs will also be monitored.

### Setting and Sample

This study is being conducted in the homes of rural women caring for persons with advanced cancer receiving services from the Saskatchewan Cancer Agency ambulatory clinics in Saskatoon and Regina and those receiving home care in the Sunrise and Regina Qu'Appelle Health Region. Women who are caregiving are a family member or significant other identified by the patient as a primary source of emotional and physical support.

Inclusion and exclusion criteria: Sample inclusion criteria for the study will be: a) female, b) 18 years of age and older, c) caring for a person who is diagnosed with advanced cancer, d) home address is outside metropolitan areas, e) English speaking and f) able to consent. Exclusion criteria include (at the time of assessment for intake to the study): a) women who are cognitively impaired, as determined by the primary oncology or home care nurse; b) otherwise unable to participate, in the opinion of the nurse and; c) caring for a person who has advanced cancer and is also diagnosed with dementia. Male caregivers are excluded because caregiver appears to have a greater impact on the health of women compared to men [20].

Sample Size: Sample size has been determined based on the requirements of the statistical methods that will be used to test the hypotheses and approximation of subject attrition rates. Path Analysis is the statistical analysis for the main hypothesis of testing the LHWP at week one and two. According to Munro [26] sample size and power calculations for Path Analysis can be made using Cohen's formulation for the most complex regression equation in the Path model. Thus, for a power of 0.80, and an alpha of 0.05, a regression equation, including 6 variables [general self efficacy, loss/grief, hope (factor1), quality of life (mental health sub score), and health services utilization (physician visits and prescriptions)] would require 98 subjects. As the study progresses, caregivers will become bereaved. The exact time and percentage of caregivers who will be bereaved is unknown. Based on Saskatoon Health Region Palliative Home Care data in the year 2001-2002, the average length of stay for palliative patients is 70 days (2.3 months) with 25% dying in 13 days, 50% in 36 days and 75% in 82.75 days. This means that approximately 50% of the subjects may become bereaved in a little over a month. In order to have sufficient numbers of subjects in both groups (active and bereaved caregivers) the sample size will be doubled to 200. Two hundred subjects would provide adequate power for the proposed analysis, so sampling will continue until this is achieved.

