### Specific Aim #1

Hypothesis #1.1 (testing of the model) will be tested with path analysis modeling. Path Analysis is a multivariate statistical technique in which a series of multiple regression models are used to test the strength of the influence, and by implication, the causal relationships between variables. Change scores will be calculated by post intervention minus baseline scores. Variables will be assessed for multi-co linearity and association. Those variables that are significantly correlated with the outcome variables will be entered into the path analysis model. Possible mediator variables such as Palliative Performance Scale (PPS) and significantly correlated caregiver demographics will be co-variants. Path Analysis will be used to test the model at 1 and 2 weeks.

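### The 98 behind the sample size counts six predictors, but the six variables listed include the outcomes and two year-long utilization counts and leave out PPS and the planned covariates, so it matches no equation fitted at weeks 1 and 2

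*Protocol article*

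**What the plan says.** Under Setting and Sample, the article sizes the study for the path analysis of the main hypothesis at weeks 1 and 2, "using Cohen's formulation for the most complex regression equation in the Path model". The inputs are "for a power of 0.80, and an alpha of 0.05" and "a regression equation, including 6 variables [general self efficacy, loss/grief, hope (factor1), quality of life (mental health sub score), and health services utilization", the last item being split into physician visits and prescriptions. The result is that this equation "would require 98 subjects". The figure is then doubled so that active and bereaved caregivers are both sufficiently represented, and the paragraph concludes: "Two hundred subjects would provide adequate power for the proposed analysis".

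Other sections describe the model to be fitted:

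- **Hypothesis 1.1 (Specific Aim #1, Background):** self-efficacy and loss/grief predict two outcomes, hope (HHI Factor 1) and the SF12 mental health score. Health services utilization is not mentioned.
- **Table 1:** for caregivers, utilization is the count in the year after enrolment minus the count in the year before.
- **Data Analysis, Specific Aim #1:** "Path Analysis will be used to test the model at 1 and 2 weeks". Also: "Possible mediator variables such as Palliative Performance Scale (PPS) and significantly correlated caregiver demographics will be co-variants".
- **Data Analysis, opening paragraph:** demographics that correlate significantly are added to the model.
- **Intervention section, on length of journaling:** "If there is a significant relationship with any of the variables it will be added to the statistical analysis of conceptual framework".
- **Data Analysis, Specific Aim #3:** utilization and the active/bereaved comparison are handled by repeated-measures ANCOVA.

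**The concern.** The method named needs the number of predictors in the most complex equation. What the paragraph supplies is a list of the conceptual model's variables, and this differs from the week-1/2 equations in three ways.

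1. The dependent variable is in the list. Whichever of the six is the outcome, no more than five can be predictors.
2. Two of the six are utilization counts that are complete only 12 months after enrolment. They cannot explain scores taken one or two weeks after baseline.
3. PPS, correlated demographics and possibly length of journaling are to enter the model, and none is counted.

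The figure 98 is the only derived number in the sample-size paragraph. The target of 200 and the statement of adequate power both follow from it. A reader who wants to know what the main analysis requires cannot learn it from this figure.

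**Working it through.** **Inputs.** Alpha 0.05, power 0.80 and six variables come from the Sample Size paragraph. The effect size is not given. I assume Cohen's medium value, f2 = 0.15 (R2 about 0.13), and show 0.10 and 0.20 as a range.

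**Formula.** Overall F-test of a regression with u predictors and N subjects: power = P(F' > Fcrit), where Fcrit is the 0.95 quantile of F(u, N − u − 1) and F' is noncentral F with the same degrees of freedom and noncentrality f2 × N. The required N is the smallest that gives power of at least 0.80.

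**Reproducing 98.** With u = 6 and f2 = 0.15, N = 98 (power 0.804; at 97 it is 0.798). Cohen's table form agrees: 13.62 / 0.15 + 6 + 1 = 97.8, rounded up to 98. The rule of thumb 50 + 8m also gives 98 with m = 6, so it too needs six predictors. With u = 5 the F-test gives 92. Five predictors reach 98 only at an unconventional f2 of about 0.139. Six predictors at a medium effect is therefore the natural reading.

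**Recounting from the plan's own model:**

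| Equation | u | N at f2 = 0.15 | N at f2 = 0.10 | N at f2 = 0.20 |
|---|---|---|---|---|
| Quality of life on self-efficacy, grief and hope | 3 | 77 | 114 | 59 |
| Same, plus PPS | 4 | 85 | 125 | 65 |
| Five predictors: the most the six-variable list allows, or PPS plus one covariate | 5 | 92 | 134 | 70 |
| PPS plus two covariates | 6 | 98 | 143 | 75 |
| PPS plus three covariates | 7 | 103 | 151 | 80 |
| PPS plus four covariates | 8 | 109 | 159 | 84 |

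The two errors pull in opposite directions. Removing the outcome and the utilization counts lowers the requirement; adding PPS and covariates raises it. At f2 = 0.15 the stated 98 is right only if exactly two covariates join PPS, and nothing in the article fixes that number.

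**Does 200 suffice for the whole-sample path model?** At N = 200 and f2 = 0.15, power is 0.998 with three predictors, 0.992 with six and 0.978 with ten. It stays at or above 0.80 up to 34 predictors. At f2 = 0.10, power with ten predictors is 0.87. If only about 150 women were available at week 2 (an illustration, taking a 25% loss), power at f2 = 0.15 stays at or above 0.80 up to 18 predictors. At f2 = 0.10 and N = 150, it is 0.82 with six predictors and 0.73 with ten.

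**The case against.** The best defence is that nothing depends on the slip. For the hypothesis as stated, 98 is generous (77, or 85 with PPS). The covariates are conditional on observed correlations and may be few, and the target is 200. All of this stands at a medium effect, and it limits the point to the derivation.

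A second defence is that Figure 1 is not shown and that the Background has quality of life influencing utilization. Utilization could then be an end point of the path model, regressed on week-1/2 scores. That is possible, but it would make utilization an outcome, and six predictors would still not follow.

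A third is that an article may leave the effect size and covariate list to the full protocol. That is fair, and their absence is not the finding. The finding is that the inputs the article does state disagree with its own hypothesis, Table 1 and analysis section.

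A reader might go further and infer from the doubling that each caregiver group needs 98 or more for this regression, so that 200 fails once the equation has more than six predictors. The documents do not support this. The Aim 1 analysis does not split the path model by bereavement. The group comparison is the Aim 3 ANCOVA at 3, 6 and 12 months. Data collection after a death resumes only after a one-month gap and only if the program was completed, so a bereaved subgroup at weeks 1 and 2 is hardly possible. Nor may a reader conclude that 98 is simply too small, since the number of covariates is unknown.

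**Conclusion.** The point holds as an error of derivation. The 98 equals the requirement for six predictors at an assumed f2 of 0.15, but the list behind it contains the outcomes of Hypothesis 1.1 and two 12-month counts and omits terms that the plan adds. The list itself supports at most five predictors (92). The planned week-1/2 equation needs 77 to 85 before demographics or journaling time, and more than 98 only from the third further covariate on (103 or more).

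The practical effect is limited. The claim that 200 is adequate is not shown to be false for the whole-sample path model: power is about 0.98 with ten predictors at f2 = 0.15. This rests on the assumed effect size and on the overall F-test as the criterion. The regression figure says nothing about whether the two caregiver groups are large enough for Aim 3, because that analysis is a different one.

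**What to change.** In the Sample Size paragraph:

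- Name the most complex equation to be fitted at weeks 1 and 2. Count its predictors without its outcome and without the utilization counts, but with PPS and the planned covariates (including length of journaling if it may enter).
- State f2, and replace 98 with the N that matches that count.
- State that 200 is adequate for this equation in the whole sample, and give the power.
- Keep the doubling as a provision for having both active and bereaved caregivers, but do not present the regression N as the requirement for each group. The group comparison is the Aim 3 repeated-measures ANCOVA.

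The cost is wording and a short recalculation. No extra subjects are needed.

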**Figure 2 F2:**
[figure not shown]
**Data Collection**.

The second visit is scheduled for 1 week after the first visit. During the second, third, fourth fifth and sixth visit data is collected as per the first visit except for the demographic form. Further, subjects are asked additional questions such as how much time they spent during the week on their hope activity. At the second visit journals are photocopied.

Each visit is about 1-1.5 hours at the maximum to prevent fatigue. A week before each visit a reminder card is mailed to the caregiver's homes. Three days before the scheduled visit the RA's will phone to remind subjects of the data collection visit. To encourage retention birthday cards, a fridge magnet with the Living with Hope Logo and a newsletter is mailed from the team.

The site collaborator is also notifying the RAs as soon as a caregiver becomes bereaved. Data collection is continuing through bereavement following a one month time lapse from the death of the care recipient if subjects have completed the LWHP. In our preliminary work with caregivers who are bereaved data collection has not caused distress. This is supported by another study whose bereaved caregivers reported benefits of participating within the first year following bereavement [25]. Data collection will take place over 28 months.

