### Specific Aim #3

Hypothesis #3.1 (patterns of GSE, RGEI/NGREGI, HHI, SF12 and HSU over time) will be tested by repeated measures 2- factor ANCOVA with between groups factor (non-bereaved versus bereaved) and a repeated-measures factor for time (3, 6, and 12 months) to describe the patterns of the scores over time. PPS and caregiver demographics that were significantly correlated will be co-variants. If the F scores are significant (p < .05) post hoc testing will be done to determine where the scores are significantly different.

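### Doubling 98 to 200 does not give about 100 per group when Aim 3 compares them: on the plan's own figures at most about 50 of 200 caregivers are active at 3 months

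*Protocol article*

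**What the plan says.** All places are in the Protocol article.

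- **Setting and Sample, sample size.** The method is that "sample size and power calculations for Path Analysis can be made using Cohen's formulation for the most complex regression equation in the Path model". The calculation is "for a power of 0.80, and an alpha of 0.05, a regression equation, including 6 variables", which "would require 98 subjects". The paragraph ties this to the path analysis at weeks 1 and 2.
- **Same paragraph, bereavement.** Regional palliative home care data give an average stay of 70 days, "with 25% dying in 13 days, 50% in 36 days and 75% in 82.75 days". The text draws from this that about half of the subjects may be bereaved in a little over a month, and adds that the exact timing and percentage are unknown.
- **Same paragraph, conclusion.** The step from 98 to 200 is explained as follows: "In order to have sufficient numbers of subjects in both groups (active and bereaved caregivers) the sample size will be doubled to 200". The paragraph then closes with a general claim about power, not limited to any one aim: "Two hundred subjects would provide adequate power for the proposed analysis". The opening sentence says attrition was taken into account, without giving a rate.
- **Specific Aim #3 (hypothesis 3.1) and its analysis section.** Active and bereaved caregivers are compared by repeated-measures ANCOVA with "a repeated-measures factor for time (3, 6, and 12 months"), tested at p < .05. No effect size or power calculation is given for this analysis.
- **Data Collection.** "Data collection is continuing through bereavement following a one month time lapse from the death of the care recipient if subjects have completed the LWHP".
- **Purpose.** Bereaved caregivers are to be kept in the study where possible and followed through bereavement.

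**The concern.** The reason given for 200 is a two-group comparison, but the number doubled belongs to a different analysis at a different time. Doubling gives about 98 to 100 per group only if the split is even when the groups are compared. The split is even near day 36. The visits are at 1 and 2 weeks and at 3, 6 and 12 months, so no visit is close to an even split, and every Aim 3 comparison falls after the quoted 75% point.

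What is at stake is how Aim 3 will be read. A non-significant difference between active and bereaved caregivers, in a study described as adequately powered, invites the conclusion that the patterns do not differ. With a small active group that conclusion would not be warranted.

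**Working it through.** **Inputs from the sample-size paragraph:** alpha 0.05, power 0.80, 6 variables, N = 98, final N = 200; deaths 25% by day 13, 50% by day 36, 75% by day 82.75; mean 70 days. **Inputs from Aim 3:** comparisons at 3, 6 and 12 months, taken as days 91, 182 and 365. **Assumptions:** f² = 0.15 for the regression and a difference of 0.40 SD for Aim 3 (the plan states neither); a two-sided test; no attrition, which favours the plan.

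**1. The plan's figure.** Noncentral F with u = 6, v = N − 7, λ = 0.15N: N = 98 gives power 0.804, so 98 reproduces. With N = 200 the same regression has power 0.99. Aim 1 is comfortable.

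**2. Active caregivers at 3 months.** Day 91 is later than day 82.75, so at most 25% are still active: 0.25 × 200 = 50. This needs no model.

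**3. Ceilings at 6 and 12 months, without a model.** The first three quarters of stays contribute at least 0.25×0 + 0.25×13 + 0.25×36 = 12.25 days to the mean. That leaves 70 − 12.25 = 57.75 days for the last quarter, where each stay is at least 82.75 days. If a share p exceeds time t:

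82.75 × (0.25 − p) + t × p ≤ 57.75, so p ≤ (57.75 − 20.69)/(t − 82.75) = 37.06/(t − 82.75), and p cannot exceed 0.25.

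- 6 months: 37.06/99.25 = 0.37, capped at 0.25, so at most 50 of 200.
- 12 months: 37.06/282.25 = 0.131, so at most about 26 of 200.

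**4. Fitted curves, as extrapolation only.** Exponential (through the median), Weibull, lognormal and log-logistic curves give about 35–47 active at 3 months, 6–24 at 6 months and 0–11 at 12 months. Their implied means run from about 52 to about 200 days against the stated 70, so they indicate direction and are not bounds.

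**5. Power, for illustration.** Two-sample t-test at one visit, δ = 0.40 × √(n₁n₂/(n₁+n₂)). Detectable difference at 80% power = (1.96 + 0.84) × √(1/n₁ + 1/n₂). All rows after the first use a total of 200.

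| Active v bereaved | Where it applies | δ | Power at 0.40 SD | Detectable difference |
|---|---|---|---|---|
| 98 v 98 | even split | 2.80 | 80% | 0.40 SD |
| 50 v 150 | ceiling, 3 or 6 months | 2.45 | 68% | 0.46 SD |
| 26 v 174 | ceiling, 12 months | 1.90 | 47% | 0.59 SD |

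The power figures in the last two rows are upper limits, because the active counts are ceilings and attrition is ignored.

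**6. Attrition.** 200 − 2 × 98 = 4 subjects, or 2% of 200. For a two-group comparison needing 98 each, this is almost no allowance.

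**7. Early bereavement.** The programme lasts two weeks and 25% of deaths fall by day 13. If stays are counted from enrolment, 0.25 × 200 = about 50 caregivers may be bereaved before finishing it. Under the completion condition in Data Collection they may then not be followed.

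**The case against.** **The bereavement figures may not fit this sample.** They come from palliative home care in one region in 2001–2002, while the study also recruits from ambulatory cancer clinics, where survival may be longer, and the plan itself calls timing and percentage unknown. This stands as a caveat on the expected counts. It does not rescue the doubling: the plan justifies 200 with these data, and the Purpose section applies the 50% figure from enrolment. It cannot use the median and set aside the 75% point beside it.

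**Aim 3 is exploratory.** Its wording is about exploring and describing patterns, and the main hypothesis is Aim 1. That lowers the weight of the point. Still, hypothesis 3.1 is a formal test at p < .05, and the power statement is not limited to Aim 1.

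**The planned analysis is not a single-visit t-test.** Covariates, change scores and repeated measures could alter power. This stands, and it is why the percentages are illustrative. They do not add active caregivers.

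**Stronger readings a reader might infer.** One is that almost no active group remains at 6 and 12 months. The documents give no quantile after day 82.75, and their quartiles and mean allow up to 50 and about 26. Another is that the plan implies a target of 0.40 SD; it states no effect size for Aim 3. A third is that Data Collection flatly contradicts Purpose; the latter promises retention only where possible, which can accommodate a completion condition.

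**Conclusion.** The adequate-power statement is wrong as written for Aim 3. On the plan's own quartiles, at most about 50 of 200 caregivers are active at the first comparison, about half of the 98 to 100 that the doubling is meant to secure. That result rests only on the quoted 75% point and on those data applying to this sample. The ceilings of 50 at 6 months and about 26 at 12 months also use the 70-day mean; lower counts depend on the chosen curve. The loss of power, from about 80% to at most about 68% and 47%, is conditional on an assumed 0.40 SD and a simple comparison.

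It does not follow that the study as a whole is underpowered, since Aim 1 keeps ample power, or that the 6- and 12-month contrasts must be abandoned. The statements on following bereaved caregivers are not a direct contradiction, but need reconciling because roughly a quarter of care recipients may die before the programme ends.

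**What to change.** 1. In the sample-size paragraph, limit the 98 and the adequate-power statement to the Aim 1 path analysis.
2. Give the expected active and bereaved numbers at 3, 6 and 12 months from the quoted quartiles, with their uncertainty and the caveat on the source population, and state the resulting detectable difference for the Aim 3 contrast after a stated attrition allowance.
3. State in Aim 3 that a non-significant active-versus-bereaved result, especially at 6 and 12 months, is not evidence of no difference.
4. Reconcile the completion condition in Data Collection with the retention statement in Purpose, and say what happens to caregivers bereaved before the two weeks end.

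Items 1 to 3 are rewording; the price is a less favourable power statement for Aim 3. Item 4 is also rewording if the condition stays. If early-bereaved caregivers were to be followed, the cost could reach about 50 × 3 = 150 further home visits. Making 3 months the only formal contrast would be a debatable trade-off, because the Purpose section seeks patterns for both groups over the year.
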